**Figure 4 F4:**
[figure not shown]
Expected error rates and sample size, by changing stopping rule threshold.

#### Interventions administered to clusters

Where the chosen intervention can only be implemented in clusters rather than randomising individuals to receive the intervention, the local management team will be convened to develop a design tailored to the intervention. An important factor to account for in any design will be determining how much the outcome varies by cluster and how large each cluster is. For cluster-level interventions, it is likely we will carry out a more traditional approach with a fixed number of clusters randomised before declaring one arm the winner. The number of clusters randomised will be based on the intracluster correlation, the current attendance rate, the size of the clusters and the effect size for which we want to be powered to detect.

### Recruitment

As the trial is pragmatic, the responsibility for recruiting screening participants lies exclusively with local programme managers. Programme implementers will enrol participants by seeking consent from all those who require referral for further assessment and care.

### Allocation

#### Sequence generation

We will use computer-generated random numbers to generate the allocation sequence and assign all consented, referred participants to intervention arms, with equal numbers of participants in each arm. Where appropriate, blocking will be used with blocks between 4 and 12. Stratification will be used where appropriate.

#### Allocation concealment mechanism

For interventions delivered to individuals, the allocation sequence will be generated within the Peek system in real time, as participants are referred. As human trial managers are not involved in allocation there is no need for concealment.

For cluster trials, these will be done randomly. Restricted randomisation will likely be used in this scenario to achieve balance between arms.

### Implementation

The algorithm will be set up, so that it can implement digital interventions such as SMS messages without human investigators being exposed to the allocation status of individual participants. For interventions that require human intervention—such as providing transport, chaperones, or physical vouchers, implementers will be informed of individual participants’ assignment status via the Peek app at the stage that intervention needs to be delivered.

### External independent review of interventions prior to implementation

As and when new interventions are selected for testing, they will need to be externally reviewed by an independent national ethics committee to ensure that the intervention(s) do not pose undue risk. The platform trial is designed to test low/negligible risk service modifications. Coupled with the fact that the master protocol will already have received ethical approval, this should enable rapid/expedited ethical review of new interventions rather than full committee review. Table 4 summarises example interventions and risk thresholds.

**Table 4 T4:** Risk thresholds and example interventions

Level of risk	Descriptor	Example interventions
High	Risk markedly higher than standard care: high probability of physical, psychological, social or economic harm	N/A
Moderate	Risk somewhat higher than standard care	N/A
Low	Comparable to the risk of standard care	Vouchers/discounts/subsidies Changes to which professional perform the screening/triage Use of different screening technologies for example, new equipment Use of different medications for example, eye drops Free chaperones or transport
Negligible	Small modifications to existing routine programme where the process of obtaining consent would introduce burdens to the patient that are greater than the intervention itself	Frequency, days, or time of day that reminder SMS messages are sent Wording of SMS communications Community sensitisation (eg, radio commercials/plays/training) Clinic days, times and locations Option to code additional eye conditions (beyond low acuity) Patient flow Information presented to programme managers, eg, access to a dashboard Types of reminders for example, SMS or picture message or voice message or leaflet

### Ethics and dissemination

Once the master adaptive platform trial (APT) has received ethics approval, individual interventions will be submitted as amendments to the master APT in the form of new appendices. Individual trials will not commence until ethics approval has been received from LSHTM and the relevant local ethics committee(s).

Each individual trial will have its own protocol that will be published online. The results of each trial will be immediately fed back to the relevant programme managers. Findings will also be shared with wider stakeholders, including eye care professionals, policymakers and community representatives at dedicated dissemination meetings. We will write-up all individual trials for publication in the peer-reviewed literature and share lay-friendly summaries via social media.

### Masking

#### Who and how

Once assigned by the algorithm, each participant’s online record will automatically update to display which arm they have been allocated to. Participants will not be masked to assignment. For interventions that require human delivery (eg, handing out a paper voucher), implementers will be able to view allocation status out of necessity. Outcome assessment will be performed by a different group—those responsible for checking-in participants at triage clinic. No steps will be taken to mask these staff to participant allocation status. Ongoing interim data analysis will be performed by the Bayesian algorithm every 72 hours.

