#### Primary outcome

The proportion of people attending triage clinic on their appointed date from the left-behind group was measured using attendance data collected by staff when people check-in.

The left-behind group will be identified at baseline as part of the ‘identify’ stage of the IM-SEEN process. This group will be constituted of the group(s) with the lowest baseline attendance rates that collectively constitute at least 10% of the total population. A focus on left-behind groups is important to programme managers who are trying to close gaps, extend health service coverage and ensure that their services do not exacerbate existing inequalities.

When referred participants check-in at ophthalmic clinics, their attendance status is recorded by administrative staff using the Peek app, which automatically updates a central database that holds records of each participant’s eye care need, sociodemographic characteristics, arm allocation and attendance status at the ophthalmic clinic on the appointed date. Our Bayesian algorithm will review the attendance data for every referred participant every 72 hours and calculate the probability of attendance within each arm. In our modelling, we have estimated that 100 people will be referred every 72 hours. This aligns with what we have observed in India and Kenya where approximately 1000 people are screened per day, of whom approximately one-third are referred. We have stipulated that the left-behind group will include at least 10% of the total population (ie, 100 people every 72 hours). In programmes where fewer people are referred every 72 hours, the interim analysis window will be extended as appropriate.

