#### Unmasking

Human investigators and programme managers will not be able to access data on allocation of participants to specific arms unless they are involved in delivering an intervention.

The Data Safety and Monitoring Committee (DSMB) will have access to all data at any point and for any reason, including to unmask assignment if required. The trial steering committee members will only be able to access these data as per the adverse event (AE) protocol outlined below.

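### Check-in staff who enter the primary outcome are left unmasked without a stated reason, although access to the arm is already limited for other roles and the default stopping rules react to small recorded differences

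*Protocol article*

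**What the plan says.** Under Masking (Who and how), the protocol article says that "each participant’s online record will automatically update to display which arm they have been allocated to". It adds that "Participants will not be masked to assignment", and that "Outcome assessment will be performed by a different group—those responsible for checking-in participants at triage clinic". Of those staff it says: "No steps will be taken to mask these staff to participant allocation status".

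The Primary outcome section says how the entry is made: "their attendance status is recorded by administrative staff using the Peek app, which automatically updates a central database". That database also holds the arm.

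Other roles are restricted. The Unmasking section states, for managers of the programme and for investigators, that they "will not be able to access data on allocation of participants to specific arms unless they are involved in delivering an intervention". Under Implementation, where people must deliver the intervention, "implementers will be informed of individual participants’ assignment status via the Peek app at the stage that intervention needs to be delivered".

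The article gives no reason for leaving check-in staff unmasked, and the Limitations section does not mention it.

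**The concern.** The primary outcome is check-in at triage on the appointed date, entered by hand by local staff. No second source for it is described. The section on non-adherence and missing data treats missing outcomes as impossible, so an entry that was not made can only count as non-attendance. If check-in were slightly more complete in one arm, or people arriving on another day were handled differently by arm, the gap would enter the primary outcome unseen.

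The stopping rules make small gaps matter. Rule 1 by default stops the trial when one arm has more than 95% probability of being best, and any difference above zero counts. The winning arm then becomes standard care. A larger sample does not remove a recording bias; it makes a declaration on it more likely.

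The article accepts a high type I error because choosing between equally good arms does little harm. That argument does not cover recording bias, which can also favour a worse arm.

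**Working it through.** **Inputs from the protocol article.** Two arms at 1:1, control attendance 50%, a look every 100 outcomes, both thresholds at 95% (Operating characteristics); default ceiling 10 000 (same section); Beta(100,100) prior per arm (Statistical methods).

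**Input not in the article.** The rate of wrong recording by arm. It is assumed and varied below.

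**Model.** With y of n recorded as attending, an arm's posterior is Beta(100 + y, 100 + n − y), with mean m = (100 + y)/(200 + n) and variance m(1 − m)/(n + 201). Let δ be the difference in posterior means and s its standard deviation (normal approximation). Rule 1 stops for the intervention when Φ(δ/s) > 0.95, and for control when it is below 0.05. Rule 2 stops when P(|difference| < 1 point) > 0.95. Results come from 3,000 to 20,000 simulated trials per setting.

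**The plan's own figures first.** The article states 92% power at d = 1%, at least 98% at d = 3% or more, and 32% false positives at d = 0. With no effective ceiling, power read as 1 − P(inferior arm wins), and false positives counted in one direction, the simulation gives 91.5%, 98.8% and 30.5%. The model therefore matches the plan's to within 2 points. Only this combination reproduces all three figures together.

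**From misrecording to a gap.** If a share w of non-attenders in one arm is recorded as attending, and none in the other, the recorded gap is w × (1 − attendance). At 50% attendance, w = 2% gives 0.02 × 0.50 = 1 point. Missing 2% of true attenders in one arm gives a gap of the same size, 0.02 × 0.50 = 1 point, against that arm.

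**Chance that the favoured arm is declared best, no true effect, 50% attendance:**

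| Assumed recorded gap (points) | 10 000 ceiling | No effective ceiling |
|---|---|---|
| 0 | 21% | 30% |
| 0.25 | 26% | not run |
| 0.5 (w = 1%) | 33% | 60% |
| 1 (w = 2%) | 48% | 86% |
| 2 (w = 4%) | 78% | 98% |
| 3 (w = 6%) | 95% | not run |

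Repeat runs under the ceiling gave 33 to 34% at 0.5 points and 47 to 49% at 1 point.

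**Variations under the ceiling.**
- At 30% attendance, w = 1% gives 0.01 × 0.70 = 0.7 points and 39%; w = 2% gives 1.4 points and 64%; w = 4% gives 2.8 points and 95%.
- With rule 1 raised to 99%, gaps of 0, 1 and 2 points give 5%, 20% and 52%.
- With rule 1 lowered to 51%, trials stop after about 100 outcomes almost at random, and a 1-point gap moves the pick only from 50% to 54%.

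**A worse arm.** If an arm is truly 1 point worse but has a 2-point recording advantage, its recorded difference is −1 + 2 = +1 point. It then wins in about 48% of trials under the ceiling. An arm that is 1 point worse and correctly recorded wins in about 8%.

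**The case against.** The strongest reply is that attendance is close to a hard fact. Table 3 shows check-in at triage as the step before the eye examination. To bias the outcome, staff would have to enter people who are absent, or examine people without entering them, and do so by arm. The article gives no reason why they would, and it separates these staff from those who deliver the intervention. The percentages come from inserting a gap and showing that the rules detect it, as they are designed to do. Masking would also help least where the arm is most visible: a paper voucher, a chaperone or arranged transport can reveal it at the desk, and a cluster-level change cannot be hidden. Finally, each individual trial has its own protocol and ethics review, where masking can be set.

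Much of this stands. The probability and size of misrecording are unknown and may be small. What does not stand is the general refusal: the master protocol declines masking for all trials, including those of SMS wording or timing, where hiding the arm would work well and would change neither care nor delivery.

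A reader might infer more than the article supports:
- **That check-in staff see the arm on their screen.** The article says the online record displays it and that these staff are not masked. The check-in view itself is not described, so this is a strong inference, not a stated fact.
- **That the two masking sections contradict each other.** They do not. One restricts investigators and programme managers, the other concerns check-in staff, and different roles may have different access.
- **That hiding the arm is free.** The article gives no cost. Existing limits by role and stage make a low cost plausible, no more.
- **That lower thresholds make the problem worse.** At 51% they do not; the argument rests on the default 95% rules.

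**Conclusion.** The point holds as a design weakness with a simple remedy. The people who enter the primary outcome are deliberately left unmasked, no reason is given, and the protocol already limits access to the arm for roles that do not record the outcome. Under the default rules, 50% attendance and the 10 000 ceiling, an assumed recording gap of 1 point raises the favoured arm's chance of winning from about 21% to 48%, and a gap of 2 points to 78%. At 0.25 points the rise is only to 26%.

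These figures rest on assumed gaps in one direction and say nothing about how often such gaps occur. No bias has been shown, and neither the sample size nor the stated power changes if the fix is made. It should be made because it removes a possible bias that the design would amplify, with little apparent downside.

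**What to change.** Replace the sentence under Masking (Who and how) that declines masking of check-in staff. Suggested text:

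*For individually randomised interventions, the arm will not be shown in the check-in view of the app wherever the intervention allows (for example, SMS wording or timing). Where clinic staff need the arm, it will be shown only after check-in has been saved. Each individual trial protocol will state which applies.*

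Add check-in staff to the roles covered under Unmasking, so that both sections describe the same access rules.

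Add a sentence to Limitations: masking of check-in staff is partial where participants carry or reveal the intervention (vouchers, transport, chaperones) and is not possible for cluster-level changes, so some risk of differential recording remains. If the sponsor keeps the present choice, the reason should be stated and the risk listed there.

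The cost is probably a small permission change in the app and a few sentences of text. The sponsor would need to confirm the software effort.

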#### Unmasking

Human investigators and programme managers will not be able to access data on allocation of participants to specific arms unless they are involved in delivering an intervention.

The Data Safety and Monitoring Committee (DSMB) will have access to all data at any point and for any reason, including to unmask assignment if required. The trial steering committee members will only be able to access these data as per the adverse event (AE) protocol outlined below.

### Data collection

#### Data collection methods

As stated above, outcome assessment (attendance at clinic) will be recorded when participants check-in at the clinic on their appointed date. Each participant’s attendance status will be recorded on their central record.

#### Retention

There are no plans to promote participant retention and complete follow-up.

#### Data management

All data entry will be performed by programme staff as part of routine screening and clinical care. See the data management plan (online supplemental appendix 1) for further information about coding, security, and storage.

### Equity analyses

The primary aim of the platform trial is improving equity. We focus on attendance rates in the left-behind group, and also look at how attendance rates in this group compare to those among the entire population.

### Non-adherence and missing data

Missing data is not a problem because the outcome is attendance. Non-adherence will depend on the intervention. We will use intention-to-treat analysis.

An independent Data and Safety Monitoring Board (DSMB) will be appointed in each country with the primary aim of assuring safety of participants in the trial(s). The DSMBs will advise the steering committee and sponsor on continuation or stopping of the trial(s) based on safety and efficacy considerations. Each DSMB will have three members, all independent of the running of the trial, and all with relevant clinical and epidemiological experience. Each DSMB will operate independently of the study sponsor and the steering committee. Each DSMB will confirm their own specific meeting arrangements and draw up their own charter, working from the template produced by the Damocles Study Group.^18^ It is proposed that each DSMB would meet prior to the beginning of each individual trial conducted under the platform protocol, one-third of the way through, and at the end of each individual trial, to assess the safety of the trial procedures. Each DSMB will agree the way it will monitor the data, what it requires from the investigators in this respect and will communicate this to the Principal Investigators (PIs). All data can be interrogated remotely in real time. The DSMB may visit the study coordination centre to assess data management, record keeping and other important activities.

### Consent

Written informed consent will be sought by screeners during screening—at the point that participants are identified as having an eye care need and referred for further care. Consent will be recorded either on paper forms or by using an electronic tick box (as appropriate for low-risk trials). Whichever format is used, consent status will be recorded on the Peek app.

Participants will be given the contact details of the research managers and will be free to leave the trial at any time. There will be no remuneration for participants. A draft consenting statement is provided as online supplemental appendix 2.

### Patient and public involvement

Lay people and community advisory committees have reviewed and contributed to the development of this protocol. These are the Pono Yame IM-SEEN advisory committee, the Kenya Vision Impact Programme IM-SEEN advisory committee, the NNJS IM-SEEN advisory committee and the [name] Eye Hospital IM-SEEN advisory committee.

The interventions that the platform trial will test will be derived from engagement with affected groups. Lay representatives will assist with interpretation and publication of the trial findings.

### AE reporting and harms

An AE is defined as any untoward medical occurrence in a patient or study participant. All AEs will be reported. Depending on the nature of the event, the reporting procedures below will be followed. Any questions concerning AE reporting will be directed to the study coordination centre in the first instance. The flowchart below has been provided to aid the reporting of AEs.

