### Discontinuing or modifying interventions

Arms will be discontinued (or modified to remove the risk) if there is evidence that they are harming exposed individuals. We note that only low/negligible-risk service modifications will be tested. Risk will be assessed at the intervention selection stage by a group of researchers, programme managers and lay representatives. Interventions that are deemed to be appropriate will also be independently reviewed by independent ethics committees in each setting before they are implemented in the platform trial.

There are no *a priori* strategies to improve adherence as we are not prespecifying the interventions.

As our trials will be embedded within routine service delivery, we cannot exclude the possibility that other initiatives will be introduced by local teams before, during or after individual trials. We will report all programmatic changes that take place during individual trials that could bias our findings.

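### Adverse events are limited to medical occurrences, so purely social or economic harm, and psychological harm short of a medical event, has no described route to the AE log or the DSMB

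*Protocol article*

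**What the plan says.** Under AE reporting and harms, the protocol article gives a single definition: "An AE is defined as any untoward medical occurrence in a patient or study participant". It adds "All AEs will be reported". The two subsections that follow rest on this term. Non-serious AEs go to the coordination centre, a dedicated log and the data and safety monitoring committee within 72 hours, with their relation to the intervention noted. Serious AEs follow a faster route on a separate form. Neither subsection mentions any other kind of harm.

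Table 4, in the section on external review of interventions, sets out the risk levels. Its top level reads "Risk markedly higher than standard care: high probability of physical, psychological, social or economic harm" and has no example interventions. Vouchers and "Free chaperones or transport" are examples at the Low level, described as "Comparable to the risk of standard care". "Wording of SMS communications" is an example at the Negligible level.

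The section on discontinuing or modifying interventions says: "Arms will be discontinued (or modified to remove the risk) if there is evidence that they are harming exposed individuals". It does not tie that evidence to AEs or to medical events. The section on types of interventions says that no pharmaceutical or medical intervention will be tested.

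**The concern.** Before a trial starts, the protocol's own description of harm spans four domains. Once the trial is running, the only described reporting system recognises one kind of occurrence, the medical kind. That is a drug-trial definition applied to a programme of mostly non-medical service changes. A message that discloses someone's referral to others, a dispute over a voucher, a fare or a day's wages lost on a wasted journey, or a safeguarding incident without injury or illness would not be an AE under it. These examples are ours; the protocol does not rank harms by likelihood.

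What is at stake is the check on the low-risk assumption. The sample size section accepts a 32% chance of a false-positive conclusion when the arms do not differ, because little or no harm is expected from choosing either, and a winning arm becomes standard care. A report of no adverse events at the end of a trial would say nothing about social or economic harm, and so could not confirm that assumption for those domains.

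**Working it through.** The point rests on no figure, so there is nothing to recompute. The check sets the stated passages side by side.

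**Step 1: what the AE definition captures.** Take the four harm types in the phrase "high probability of physical, psychological, social or economic harm" and ask of each whether it is a medical occurrence.

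| Harm type in Table 4 | Meets the AE definition? |
|---|---|
| Physical | Yes, for example an injury during assisted transport |
| Psychological | Only where it amounts to a medical event |
| Social | Not unless it also produces a medical event |
| Economic | Not unless it also produces a medical event |

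**Step 2: whether any other described system records the rest.**
- The study setting section lists what the app collects: visual acuity, socioeconomic status, referral and attendance. None of these records a harm.
- The retention section plans no steps to promote complete follow-up, so no later contact is described at which harm might be noticed.
- The consent section gives participants the research managers' contact details, but does not describe this as a harms channel or link it to the log.
- The DSMB text gives each board a participant-safety aim, lets it agree what it requires from investigators, and allows real-time access to all data. This permits a board to ask for non-medical harms. It does not have them collected by default, and real-time access reaches only data that have been recorded.

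**Step 3: what this means for the discontinuation rule.** The rule acts on evidence of harm of any kind. For physical harm, and psychological harm that reaches medical level, the AE log supplies that evidence. For the remainder, no routine source is described. Evidence could still arrive informally or at a board's request, so the rule can operate, but without a regular feed.

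**Step 4: fit with the interventions.** Most named examples (vouchers, messages, chaperones, transport, clinic times and places) are non-medical. Not all are: the Low row of Table 4 also lists different medications such as eye drops, and different screening technologies, and elsewhere differing acuity thresholds are mentioned. The medical definition suits those and should stay. The gap is that it stands alone.

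**The case against.** The strongest reply has several parts.

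- **Where the four harm types appear.** They stand only in the High descriptor, which has no listed interventions. A reader might infer that Table 4 grades every intervention on four separate domains. It does not: Low is set against standard care, and Negligible turns on the burden of seeking consent. This stands. Even so, the High row is the only place where the table says what harm consists of, and it does so more broadly than the AE definition.
- **Other routes exist.** A reader might infer that non-medical harms can never be reported, or that the discontinuation rule cannot be triggered by them. Neither is supported. The rule is open to any evidence, each DSMB can set its own requirements, and participants have contact details. What remains is that these routes are discretionary or incidental.
- **Likelihood and volume.** A reader might infer that non-medical harms are the likeliest ones, or that the DSMB will be swamped by unrelated illness. The protocol ranks no harms, gives no event rate and describes no active solicitation of AEs, so neither inference has a basis here. The log also records relation to the intervention, so unrelated events can be separated.
- **Expedited ethics review.** This rests on risk judged in advance and on prior approval of the master protocol. It does not depend on AE data gathered later, so the gap does not undermine it.
- **Material not shown.** The AE flowchart, the supplementary figure on SAEs, the DSMB charters and the individual trial protocols are not available, and any of them might provide for non-medical harms. This limits how far the absence of a route can be asserted. It does not alter the definition, which the article states in full and which would then need to agree with those documents.

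**Conclusion.** The point holds as an inconsistency between three stated passages: a medical-only AE definition, a description of harm covering four domains, and a discontinuation rule open to any harm. Followed as written, the plan sends no purely social or economic harm, and no psychological harm below a medical event, to the AE log or the DSMB as a matter of routine. In size, one of the four harm types is covered, one is covered in part, and two are covered only when a medical event accompanies them.

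The effect is on safety monitoring and on what a clean safety report can be taken to show. It changes no estimand, stopping threshold, sample size, power or error rate. The conclusion assumes that the term medical carries its ordinary meaning and that the documents not shown do not already extend the definition. It does not say that such harms are common, that they could never come to light, or that an arm causing them could not be stopped.

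**What to change.** Reconcile the AE definition with Table 4 and with the section on discontinuing or modifying interventions. Keep the present definition of a medical AE, and add beside it a category along these lines: an untoward psychological, social or economic occurrence, including a confidentiality or safeguarding incident, that is plausibly related to the intervention or to trial procedures. Record it in the existing AE log with one extra field for the category, report it to the DSMB, and tabulate it by arm. The sponsor should state the reporting times for the new category, which the documents do not settle.

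Unrelated medical events should continue to be logged. Participants and those who deliver interventions by hand are not masked, so confining medical AEs to those judged related would lose a comparison between arms that does not depend on attribution.

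The cost is a short change of wording, one log field and slightly more logging. The added category carries its own weakness: relatedness will be judged by staff who may know the allocation, so differences between arms in that category need cautious reading.
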